### Participants

We will recruit 90 participants from the third Affiliated Hospital of Changchun University of Chinese Medicine (Changchun, China). Before treatment, we will perform glycosylated hemoglobin A1 (HbA1c) tests, blood lipid profile indices (total cholesterol (TC), triglycerides (TGs), high-density lipoprotein cholesterol (HDL-C), and low-density lipoprotein cholesterol (LDL-C)), fMRI screens and scale assessments for the participants to select the patients to be included. For outpatients who meet the inclusion and exclusion criteria and wish to participate in the study, we will fully communicate with patients and their family members face-to-face about the trial to ensure that the patients are able to participate throughout the study.

### Recruitment

To recruit participants, we will publicize the study through recruitment posters, scrolling electronic screens, leaflets, and WeChat public platforms. During the recruitment process, we will fully communicate with patients, clearly informing them of the purpose, significance, trial process, treatment method, and possible benefits and risks of this study. Then, we will inform patients and their guardians of the contents of the informed consent form one-by-one. When patients and their guardians completely agree with all the items in the consent form, they will sign it of their own free will.

### Inclusion criteria

Eligible participants for DCI subjects should meet the following inclusion criteria: (1) the 2020 American Diabetes Association Standards of Medical Practice for diabetes with a duration of ≥ 2 years; (2) signs or symptoms of memory loss; (3) Montreal Cognitive Assessment Scale (MoCA) score < 26 points, Clinical Dementia Rating (CDR) ≥ 0.5 points; (4) activities of daily living (ADLs) not significantly affected, and instrumental ability of daily living (IADL) score ≥ 16 points; (5) aged 50–70 years, with more than 6 years of education, able to complete a cognitive assessment; (6) sufficient visual and auditory discrimination to undergo neuropsychological testing; (7) no evidence of infection, infarction, or other focal injury, or associated clinical symptoms, as detected by transcranial CT or MRI in the 12 months prior to screening; allows for white matter lesions or cavitary infarcts in noncritical brain regions without affecting the subject’s cognitive function; and (8) signed informed consent, volunteered to participate in the study, and were able to cooperate with the physician in completing the clinical study. Eligible participants who meet the following inclusion criteria as healthy subjects: (1) conditions such as age and education that are comparable to other groups of subjects; (2) absence of significant neurological foci and absence of associated disorders that could cause cognitive impairment, as determined by cranial MRI; (3) no religious beliefs, no bad habits, such as tobacco, alcohol, coffee, and tea; (4) no job or life stress during the observation period; (5) in good health, free of cardiovascular and other organic diseases; (6) total MoCA score ≥ 26 points; and (7) signed informed consent, volunteered to participate in the study, and were able to cooperate with the physician in completing the clinical study.

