At present, the exact pathogenesis and effective treatment methods of DCI are in the exploratory stage. There is no specific Western medicine for the effective treatment of DCI, and there is a lack of clear drug intervention methods. Acupuncture is an important method for the prevention and treatment of DM and its complications, which can control blood glucose and regulate brain activation areas and abnormal brain functional connections. Studies have confirmed that acupuncture combined with metformin therapy can more effectively improve the level of fasting blood glucose in patients with T2DM [13]. Many studies have found that acupuncture can alter the changes in brain regions and functional connectivity related to cognition in patients with AD and MCI [14–16]. Therefore, in this proposed study, we aimed to (1) carry out a randomized, pseudocontrolled clinical trial comprehensively using multimodal brain imaging techniques to reveal the changes in brain structure and function in patients with DCI, (2) clarify the brain function network effect of “Adjust Zang-fu and Arouse Spirit” electroacupuncture to prevent and improve cognitive dysfunction in patients with DCI, and (3) analyze the correlation between the changes in clinical cognitive function and the changes in brain structure and function.

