### Statistical analysis

#### Clinical data analysis

Statistical analysis of the clinical outcomes will be performed using SPSS 24.0 statistical software. All statistical tests will be bilateral, and *p* < 0.05 will be considered statistically significant. For clinical information, data will be presented as the mean ± standard deviation. Student’s *t* test and the chi-square test will be used to compare group differences at baseline. A paired *t* test will be used to compare the clinical outcomes within the groups. Analysis of variance and the Wilcoxon rank-sum (if normality is violated) will be used to compare the clinical feature changes between groups. The clinical data, including MoCA, CDR, HbA1c, TC, TGs, HDL-C, and LDL-C, will be converted to domain z scores for correlational analysis with imaging data. Missing data for the primary outcome will be imputed using the multiple imputation method.

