#### Neuroimaging data analysis

Neuroimaging data processing and statistical analysis were carried out by the individualized Neuroimaging Research Laboratory of Martinos Neuroimaging Center, Massachusetts General Hospital, Harvard Medical School, USA.

The structural MRI data will be analyzed using the VBM toolbox within SPM12. The steps include interlayer time difference correction, spatial difference correction, head motion correction, standardization, and Gaussian smoothing. In the head motion correction process, the images of the subjects whose translation is less than 1 mm and rotation movement is less than 2° will be involved in the follow-up analysis. The fMRI data will be analyzed using the CIVET-pipeline toolbox and SurfStat in MATLAB 2018b. The steps include removing high-frequency components by a bandpass filter, removing the average signal of the whole brain and the signals of the ventricle and white matter, and then registering the data to the surface space of FreeSurfer. T tests and repeated-measures analysis of variance will be conducted to investigate the differences in brain regions in each group. Pearson correlation analysis will be used to test the correlation between fMRI data and clinical variables. According to the results of MRS scanning, the concentration of target metabolites will be statistically analyzed. A paired *t* test will be used to compare within the groups. Analysis of variance and the Wilcoxon rank-sum (if normality is violated) will be used to compare between groups.

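### Any imaging comparison of DCI patients with healthy subjects is non-randomised, protected only by an undefined age and education comparability, and the named tests do not adjust for either

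*Protocol article*

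**What the plan says.** All references are to the protocol article.

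- **Inclusion criteria.** DCI patients must be "aged 50–70 years, with more than 6 years of education, able to complete a cognitive assessment" and have a MoCA below 26. Healthy subjects have a separate list. Its age and education entry reads only "conditions such as age and education that are comparable to other groups of subjects", and its cognitive entry is "total MoCA score ≥ 26 points".
- **Background, aim 1.** The trial is to "reveal the changes in brain structure and function in patients with DCI".
- **Clinical data analysis.** "Student’s *t* test and the chi-square test will be used to compare group differences at baseline". "All statistical tests will be bilateral", at p < 0.05.
- **Neuroimaging data analysis.** "T tests and repeated-measures analysis of variance will be conducted to investigate the differences in brain regions in each group". Metabolite concentrations are compared between groups by analysis of variance or, without normality, the rank-sum test. No covariate is named.
- **MoCA description.** The score depends on education, and one point is added below 12 years of schooling. That correction acts on the score, not on imaging.
- **Sample size estimation.** Three groups of 30.
- **Who the controls are.** The abstract and Setting of the study say that participants are randomly assigned to intervention (60) or control (30), and the abstract has all participants continuing hypoglycemic therapy. The randomization section assigns only to electroacupuncture or sham, and the blood glucose section covers only those two groups. The inclusion criteria add healthy subjects.

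**The concern.** Aim 1 asks how the brain in DCI differs, and the healthy subjects appear to be the reference for that. Selecting the groups on opposite sides of a MoCA cut-off rules out randomisation between them, so age and schooling must be balanced by recruitment or handled in the analysis.

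The recruitment rule describes a group result: it cannot be applied to one volunteer at screening, and it has no margin by which to judge the group afterwards. The analysis, as named, has no term for either variable. The protocol gives some reason to expect both to matter: it says that MoCA varies with education and places DCI between brain aging and dementia. Neither statement gives the size of an age or education effect on imaging.

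At stake is the reading of aim 1. An age or education gap could appear as a regional or metabolite difference and be taken for disease.

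**Working it through.** **Inputs from the document.** Group sizes: the sample size section inflates 24 for 20% loss, 24 / (1 − 0.20) = 30, and 3 × 30 = 90, which reproduces its totals. The healthy group of 30 can be set against one DCI arm (30 v 30) or both (60 v 30). Tests are two-sided at 0.05.

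**Assumed inputs (the document gives none).** A true age gap of 0.5 SD, with 0.3 SD as a smaller case; an age-imaging correlation r of 0.3 to 0.6; no disease effect; normal data with equal variances.

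**Step 1: how often a baseline t test misses the gap.** The test follows a noncentral t distribution with noncentrality d × √(n₁n₂/(n₁+n₂)) and n₁+n₂−2 degrees of freedom.

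- 30 v 30, d = 0.5: 0.5 × √15 = 1.936; critical value 2.002 (58 df); power 0.478; missed 52%.
- 60 v 30, d = 0.5: 0.5 × √20 = 2.236; critical value 1.987 (88 df); power 0.599; missed 40%.
- d = 0.3: missed 79% and 74%.

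**Step 2: false positives in the unadjusted imaging test, all trials.** With both variables scaled to SD 1, an age gap of 0.5 shifts the imaging contrast by r × 0.5 SD. Putting that shift into the step 1 formula gives the rejection rate:

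| r | shift (SD) | 30 v 30 | 60 v 30 |
|---|---|---|---|
| 0.3 | 0.15 | 8.8% | 10.2% |
| 0.5 | 0.25 | 15.9% | 19.8% |
| 0.6 | 0.30 | 20.8% | 26.4% |

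Simulation with 8,000 trials per setting puts the largest value at 26.5%.

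**Step 3: only trials in which the baseline age test was not significant.** In the same simulation the unadjusted test rejects in 5.3 to 8.7% of these trials, and the mean remaining age gap is 0.28 to 0.31 SD. With age as a covariate the rejection rate is 4.6 to 5.4%. A repeat with 40,000 trials per setting gave 5.8 to 8.3% unadjusted and 4.8 to 5.1% adjusted.

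Education was not simulated. The same algebra applies to it for the same assumed gap and correlation.

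**The case against.** The best reply is that much of this is inferred.

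- **The contrast is not named.** The neuroimaging section specifies no DCI-versus-healthy test, and its software (SPM12, SurfStat) can take covariates that a fuller plan may list. This stands as a limit: a reader might infer that an unadjusted disease contrast is fixed in the plan, and the text does not go that far. But the tests it does name have no age or education term, and t and rank-sum tests cannot take one.
- **The baseline test is not the comparability rule.** A reader might infer that p > 0.05 is the criterion for accepting the healthy group. The document never links the two, and the t test may be meant only for electroacupuncture against sham. The miss rates therefore show only that such a test would not establish comparability.
- **The harm is smaller in trials that look balanced.** The figures up to 26% include trials where the gap was detected. In those that pass, the rate is about 5 to 9%. This stands. The full range still matters because the protocol states no action if the baseline test is significant.
- **Losses do not change the baseline check.** A reader might redo step 1 at 24 per group. The 20% loss is expected during treatment, so enrolled numbers apply.
- **An age range is implied.** Being comparable to groups bounded at 50 to 70 does imply something, but gives no tolerance and no rule for an individual.
- **The controls may not be healthy at all.** The article contradicts itself here. If they are the healthy subjects listed, MoCA eligibility makes them non-randomised.

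**Conclusion.** The point holds in a limited form. Any DCI-versus-healthy imaging or MRS contrast serving aim 1 is non-randomised by its eligibility criteria, its only stated protection is an undefined comparability, and the methods named do not adjust for age or education. For an assumed 0.5-SD age gap and a correlation of 0.3 to 0.6, false positives are about 9 to 26% over all trials and about 5 to 9% among those passing a baseline test, against about 5% with adjustment. All these rates rest on assumed values, and the contrast itself is inferred.

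The documents do not show that a gap will occur or that the imaging results will be confounded. A reader might also extend the concern to the treatment effect; that is not supported, because electroacupuncture and sham are compared by randomisation. The change is worth making because it improves a stated method at almost no cost.

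**What to change.** 1. **Analysis.** Analyse every DCI-versus-healthy imaging and MRS comparison with a linear model (ANCOVA, or the general linear model in SPM or SurfStat) that includes age and years of education.
2. **Baseline.** Report standardised differences in age and education between DCI and healthy subjects, and state that comparability is not concluded from baseline p values.
3. **Eligibility.** Keep the comparability requirement and add the patients' limits (50 to 70 years, more than 6 years of education) for healthy subjects still to be recruited. The limits should not replace the requirement: healthy subjects near 50 and patients near 70 would both satisfy them.
4. **Control group.** Reconcile the abstract and Setting of the study (controls randomly assigned; in the abstract, all participants on hypoglycemic therapy) with the healthy-subject criteria and the two-group randomization section.

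**Cost.** Two degrees of freedom and revised wording. Eligibility already requires age and education to be known in both groups, and the MoCA correction also needs schooling. The added limits may slightly narrow the pool of healthy volunteers. No extra participants or procedures are needed.

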### Exclusion criteria

Participants meeting any of the following criteria will be excluded: (1) sensitivity to acupuncture; (2) subjects with significant auditory, visual, or speech impairments affecting cognitive function testing; (3) acute complications of diabetes such as diabetic ketoacidosis and hypertonic coma within the last 3 months, and significant cardiopulmonary, hepatic, renal, and hematologic diseases that may affect cognitive function; (4) history of previous cerebrovascular disease such as cerebral infarction, cerebral hemorrhage, or other focal injury that affects cognition; vascular dementia (Hachinski Ischemia Index score ≥ 7 points) and neurological disorders that can cause dementia such as Alzheimer’s disease and Parkinson’s disease; history of severe traumatic brain injury with persistent neurological deficits or known structural brain abnormalities; (5) depression within the past 2 years with an Anxiety Self-Assessment Scale (SAS) or Depression Self-Assessment Scale (SDS) score > 50 points; (6) history of alcohol, tobacco, drug abuse, or dependence within the past 2 years; (7) use of medications in the following categories within 30 days prior to screening for cognitive impairment: medications for Alzheimer's disease or dementia, antiparkinsonian medications, short-acting anxiolytics, neuroleptic or analgesic medications, antiepileptic medications, hormones, or medications with significant cholinergic or anticholinergic side effects; (8) more pronounced cerebral white matter lesions or cavitary infarction (subject’s age-related white matter change (ARWMC) score ≥ 2 points); and (9) contraindications to MRI (claustrophobia, pacemaker implants or surgical metal plate in the body).

### Withdrawal criteria

Participants meeting any of the following criteria will be withdrawn by the unanimous decision of the two researchers: (1) participant’s decision to drop out of the study at any time for any reason; (2) death or other major adverse events or accidents occur due to disease development; (3) participants display poor compliance with the clinical trial protocols, an unwillingness to continue in the study, or requests to withdraw from the study; and (4) participants are noncompliant with the prescribed treatment, are not treated as prescribed, or have incomplete observation data affecting the evaluation.

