### Randomization, concealment of allocation, and blinding

Participants who meet the inclusion criteria will voluntarily sign an informed consent form and will be eligible for random assignment. They will be assigned randomly to the “Adjust Zang-fu and Arouse Spirit” electroacupuncture group or sham electroacupuncture group. The randomization sequence will be generated by a statistician not involved in the intervention or outcome evaluation using IBM® SPSS® Statistics version 24.0 (IBM Research Corporation, USA). The randomization numbers and group assignments will be sent immediately to the independent assessor by another research coordinator via an encrypted electronic file. As much as possible, evaluators will be prevented from communicating with the patients to avoid bias. This process will ensure that randomization concealment will be competent and unaffected by the participants or practitioners.

Due to the particularity of electroacupuncture therapy, double-blinding of the therapist and patient is not feasible. Before signing the informed consent form, patients will be told that they will receive electroacupuncture treatment. Participants will be unaware of their treatment assignment. The therapist will not be blinded but will not assess the effectiveness of the treatment. Outcome assessors, data managers and statisticians will be blinded to treatment allocation. Prior to the start of the trial, all researchers will be trained to ensure the successful implementation of the blinding procedure.

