### Sample size estimation

The sample size was calculated based on the MoCA scale score as the primary outcome. The sample size was calculated based on the noninferiority comparison of the two groups: *α* = 0.025, 1−*β* = 0.80, *Δ* = − 0.1, which was calculated by PASS software with *n* ≈ 24. Because there was partial shedding in the treatment process, the shedding rate was 20%, and thus, it was appropriate to increase the sample size and take *n* = 30 cases per group. Therefore, 30 cases per group were needed, totaling 90 patients in 3 groups.

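### Researchers may withdraw randomized participants for noncompliance, treatment deviation or incomplete data, which ends outcome collection on post-randomization grounds and fits badly with the planned multiple imputation

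*Protocol article*

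**What the plan says.** Under Withdrawal criteria, anyone who meets a listed criterion "will be withdrawn by the unanimous decision of the two researchers". Criterion 1 covers the participant's own decision to leave, and criterion 2 covers death and major adverse events or accidents. Neither is in dispute. Criterion 3 adds that "participants display poor compliance with the clinical trial protocols", next to unwillingness to continue. Criterion 4 is met when "participants are noncompliant with the prescribed treatment, are not treated as prescribed, or have incomplete observation data affecting the evaluation".

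Under Clinical data analysis the plan states: "Missing data for the primary outcome will be imputed using the multiple imputation method".

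Three other sections bear on this:

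- **Randomization, concealment of allocation, and blinding.** The randomized comparison is electroacupuncture against sham. Outcome assessors, data managers and statisticians are blinded, but of the therapist it says: "The therapist will not be blinded but will not assess the effectiveness of the treatment". It does not say who the two deciding researchers are or whether they are blinded.
- **Sample size estimation.** About 24 per group are needed, raised to 30 for an expected loss of 20%.
- **Setting of the study.** Assessments are at baseline, 4 and 8 weeks after randomization, and 1, 2, 3 and 6 months after treatment.

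**The concern.** Noncompliance and deviation from the prescribed treatment can arise only after allocation. They may also differ by arm: one arm has skin penetration, manipulation to obtain de qi and current, and the other has blunt needles that do not penetrate and no current. Criteria 1 and 3 already deal with people who want to leave. Criterion 4 therefore reaches people who may be willing to stay, including those whose treatment departed from the prescription through no choice of their own. Whether incomplete data affect the evaluation is a judgement, and the text gives no assurance that it is made blind to arm.

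Two things are at stake. The first is outcome data that later analysis cannot recover, because the assessments will not have been made. The second is the electroacupuncture against sham comparison, if the people removed differ between arms in number or prognosis.

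**Working it through.** **1. What the rule ends.** Criteria 1 and 3 speak of dropping out of, or continuing in, the study. The natural reading is therefore exit from the study, not only from needling. There are 1 + 2 + 4 = 7 evaluations. A participant withdrawn between baseline and week 4 would lose 7 − 1 = 6 of them, and one withdrawn between weeks 4 and 8 would lose 7 − 2 = 5.

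**2. The rule beside the imputation plan.** A participant with incomplete primary-outcome data can be both a ground for withdrawal and a case for imputation. There are two readings:

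- Withdrawn participants are left out of the analysis. The comparison is then not as randomized, and imputation acts only on gaps too small to trigger withdrawal.
- Withdrawn participants are imputed. The two sections then agree formally, but the rule has created the missing values, and a standard imputation that assumes missing at random does not guard against removal tied to unrecorded prognosis.

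The article does not say which applies.

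**3. The plan's own figure.** 24 / (1 − 0.20) = 30 per group, as stated. The expected loss is 30 − 24 = 6 per arm. This is loss for any reason, and the share due to the disputed grounds is not given.

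**4. Bias if withdrawn participants are excluded.** Let p be the proportion withdrawn in an arm, and d the outcome of those withdrawn minus that of those retained, in SD. The retained mean differs from the full-arm mean by −p·d, so

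bias (electroacupuncture minus sham) = −(p_E·d_E − p_S·d_S).

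All values of d, and the split of p by arm, are assumptions:

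| p_E | p_S | d_E | d_S | Bias (SD) |
|---|---|---|---|---|
| 0.20 | 0.20 | −0.5 or −1.0 | same as d_E | 0 |
| 0.20 | 0.10 | −0.5 to −1.0 | same as d_E | 0.05 to 0.10 |
| 0.20 | 0.20 | −0.5 to −1.0 | 0 | 0.10 to 0.20 |
| 0.20 | 0.20 | 0 | −0.5 to −1.0 | −0.10 to −0.20 |

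**5. Effect on the false-benefit rate (third row).** With 24 retained per arm, SE = √(2/24) = 0.289 SD. The rate is P(Z > 1.96 − bias/SE):

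- Bias 0.1: P(Z > 1.96 − 0.346) = 5.3%.
- Bias 0.2: P(Z > 1.96 − 0.693) = 10.3%.
- Without bias: 2.5%.

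**6. Precision.** The detectable difference at 80% power and two-sided 0.05 is (1.960 + 0.842)·√(2/n). This is 0.81 SD with 24 per arm and 0.72 SD with 30. The second figure is the best case, since some of the 20% will be lost for other reasons.

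**The case against.** The strongest objection is that nothing in the article excludes withdrawn participants from the analysis. The Withdrawal criteria section defines no analysis population and does not say that collected data are discarded. Analysis sets are commonly left to a statistical analysis plan, which is not shown. This stands. A reader might infer that the trial will compare only those who completed real treatment with those who completed sham, but the documents do not say so. The increase from 24 to 30 does not show it either, because allowing for dropout is routine under any analysis set.

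A reader might also infer a flat contradiction with multiple imputation. It is one only if withdrawn participants are left out. If they are imputed the sections are compatible, and in either case smaller gaps over seven evaluations remain to be imputed.

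Nor does the article report or expect different compliance by arm. Visit burden is identical (40 sessions over 8 weeks in both), participants are unaware of assignment, and the decision must be unanimous. That the two researchers are unblinded is likewise not stated; their status is simply not given. The bias figures assume that all 20% loss falls under the disputed grounds, that selection is one-sided and that no imputation is done. These limits stand, and they make the size conditional.

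What the objection does not remove is the rule itself. It operates while the trial runs, and no later choice of analysis set can supply assessments that were never made. That the trial is a pilot lowers the stakes, but the pilot is meant to inform later trials.

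**Conclusion.** The point holds as a defect in a stated rule. Criteria 3 and 4 end outcome collection on post-randomization grounds, by the judgement of two people not said to be blinded, and the article does not settle how such participants are treated in the analysis.

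Bias in favour of electroacupuncture is possible but not shown. It is zero when withdrawal and prognosis match across arms, and it would run against electroacupuncture if the selection fell on the sham arm. The 0.1 to 0.2 SD, with a false-benefit rate of about 5% to 10%, is an illustration. It rests on 20% being withdrawn and excluded, on an assumed deficit of 0.5 to 1.0 SD among electroacupuncture withdrawals, and on random sham withdrawals. The loss of scheduled assessments needs none of these assumptions. It follows from reading withdrawal as leaving the study.

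**What to change.** - In Withdrawal criteria, separate stopping study treatment from leaving the study. Delete noncompliance, treatment deviation and incomplete data as grounds for leaving the study. Leave criteria 1 and 2, and the rules for when treatment stops, unchanged.
- Keep assessing these participants at the scheduled visits unless they refuse further follow-up or cannot be assessed.
- In Clinical data analysis, state that all participants randomized to electroacupuncture or sham are analysed in their assigned arm, with multiple imputation for primary-outcome data still missing.
- Report an analysis of compliant participants as a sensitivity analysis.

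The cost is a change of wording, follow-up at visits already on the schedule, and a slightly diluted effect estimate, because participants who were not treated as prescribed stay in their arm. The trial is under way, and assessments missed under the present rule cannot be recovered, so the change is worth making early.
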